## 1. ABSTRACT

**Introduction:** Paediatric cardiac arrest (PCA), despite its low incidence, has a high mortality. Its management is complex and deviations from guideline recommendations occur frequently. We developed a new interactive tablet app, named PediAppRREST, to support the management of PCA. The app received a good usability evaluation in a previous pilot trial. The aim of the study is to evaluate the effectiveness of the PediAppRREST app in reducing deviations from guideline recommendations in PCA management.

**Methods and analysis:** This is a multicentre, simulation-based, randomized controlled, three-parallel-arm study. Participants are residents in Paediatric, Emergency Medicine, and Anaesthesiology programs in Italy. All 105 teams (315 participants) manage the same scenario of in-hospital PCA. Teams are randomized by the study statistician into one of three study arms for the management of the PCA scenario: 1) an intervention group using the PediAppRREST app; or 2) a control group (CtrlPALS+) using the Paediatric Advanced Life Support (PALS) pocket reference card; or 3) a control group (CtrlPALS-) not allowed to use any PALS-related cognitive aid. The primary outcome of the study is the number of deviations (delays and errors) in PCA management from PALS guideline recommendations, according to a novel checklist, named c-DEV15plus. The c-DEV15plus scores will be compared between groups with a one-way ANOVA model, followed by the Tukey-Kramer multiple comparisons adjustment procedure in case of statistical significance.

**Ethics and dissemination:** The Ethics Committee of the University Hospital of Padova, coordinating centre of the trial, deemed the project to be a negligible risk study and approved it through an expedited review process. The results of the study will be disseminated in peer-reviewed journals, and at national and international scientific conferences. Based on the study results, the PediAppRREST app will be further refined and will be available for download by institutions/health care professionals.

**Trial registration number:** NCT04619498

## 2. INTRODUCTION

Paediatric cardiac arrest (PCA), despite its low incidence, is associated with high mortality and serious clinical sequelae.[1-5] The need for multiple rapid and complex interventions and the etio-pathogenic differences with adult cardiac arrest, make its management challenging and error prone. International scientific societies periodically release and update evidence-based guidelines outlining the recommended management of in-hospital and out-of-hospital PCA.[6-11] The Paediatric Advanced Life Support (PALS) course has been created by the American Heart Association (AHA) to train healthcare professionals in the advanced management of PCA.[12] Nevertheless, studies demonstrated that, despite training, deviations from guideline recommendations often occur in PCA management,[13-19] and lead to patients' worse clinical outcomes.[20,21]

Previous studies have assessed multiple strategies and tools to cognitively support providers to deliver optimal resuscitation during CA, as per guideline recommendations, showing variable efficacy.[22-36] Most of these studies focused on adult cardiopulmonary resuscitation (CPR) in an out-of-hospital setting and assessed pre-recorded audio/video support or contact by phone with a medical dispatcher.[32] Several studies have so far focused on technology developed to improve the quality of chest compressions through audio/visual feedback.[33-36] Software and apps for mobile phones, and tablets, as well as augmented reality glasses have been developed and used to improve adherence to guidelines.[23-31] However, most of these tools are directed to adult CA and showed to be associated with only partial improvements in the management of simulated CA scenarios. In addition, their usability and associated perceived workload has not been formally assessed before testing their efficacy. Overall, there is very limited experience on the usefulness of interactive cognitive support through an app in the management of PCA.[31]

We developed and refined a new audio-visual interactive app for tablets, named PediAppRREST, to support the management of PCA.[37] The app was developed based on the results of a multicentre observational simulation-based study, conducted by our research team, evaluating errors and delays in the management of a PCA scenario by paediatric residents.[38] We also tested the app usability in a pilot simulation-based study of non-shockable PCA scenarios, managed by paediatric residents, all PALS certified providers. The app received good usability evaluations and it did not increase the team leader's perceived workload compared to the control group that did not use any cognitive support tool.[37] No app that has previously been tested for usability and associated perceived workload, has so far been evaluated in a large,

appropriately powered, randomized clinical trial, involving physicians from different medical specialties, for its efficacy in guiding the management of PCA.

### **2.1 Objectives**

The primary objective of this study is to determine, in a multicentre, randomized controlled trial, whether the use of the PediAppRREST app is associated with a reduction of deviations from international guidelines, in the management of a simulated PCA scenario, compared with the use of the PALS pocket reference card or with the use of no cognitive aid.

The secondary objectives are to further evaluate the usability of the PediAppRREST app and its impact on team members' workload, CPR quality, time to performance of critical resuscitation interventions, and overall team performance.

## **3. METHODS AND ANALYSIS**

### **3.1 Study design and settings**

The study is a national, multicentre, superiority, 3-parallel-group, randomized-controlled trial conducted in the setting of off-site intermediate-fidelity simulation. The study has been designed following guidelines for health care simulation research.[39] The study includes an intervention arm (PediAppRREST arm) and two control arms (CtrlPocketPALS+ and CtrlPocketPALS-). In the intervention arm participants use the novel interactive cognitive support tool, the PediAppRREST tablet app, to manage a standardized simulated scenario of PCA while the teams in the control arms manage the same scenario without the support of the app. Participants in the CtrlPocketPALS+ arm use the current recommended cognitive support tool, the PALS pocket reference card, while in the CtrlPocketPALS- arm no cognitive aid is used. The study design diagram is available in Figure 1. All the scenarios are video-recorded and reviewed by two previously trained and independent reviewers who will collect the data in the study Case Report Forms (CRFs).

### **3.2 Participants**

Participants are recruited from medical residency programs in Paediatrics, Emergency Medicine and Anaesthesiology, at the i) University Hospital of Padua, University of Padua (Padua); ii) Meyer University Hospital, University of Florence (Florence); iii) Maggiore della Carità University Hospital, University of Piemonte Orientale (Novara); and iv) Agostino Gemelli University Hospital, Catholic University of Sacred Heart (Rome).

[figure not shown]

Figure 1. Study design diagram

Eligibility of potential participants is assessed by the study investigators of each participating site. Residents must meet all the following criteria to be enrolled in this trial: i) to be attending a residency training program in Paediatrics, Anaesthesiology or Emergency Medicine; ii) to be BLS (Basic Life Support) or P-BLS (Paediatric-Basic Life Support) or PALS or ALS (Advanced Life Support) or ACLS (Advanced Cardiac Life Support) certified, following the AHA or the European Resuscitation Council (ERC) recommendations; and iii) to give consent to participate to the study and to be video-recorded. Additionally, to be eligible for the role of team leader residents must be PALS-certified according to AHA or ERC guidelines. Residents who took part in the pilot study of the PediAppRREST app,[37] or who are unable to attend the simulation sessions because of maternity/paternity leave, sick/personal leave or training abroad are not eligible to participate in the trial.

### **3.3 Randomization, allocation concealment, and blinding**

Participants are randomized by the study statistician in teams of three, stratified by study site and residency program specialty. Randomization is conducted assuring that in every team there will be at least one PALS-certified team member assigned to the role of team leader. The same statistician assigns a unique team identification number to each team and prepares the list of participants associated with each team to be sent to the principal investigators. Participants are randomly divided in teams of three members per each scenario; the team leader is selected among PALS-certified residents whereas the other two members have to be at least BLS-certified. The teams are randomized with a 1:1:1 ratio in the intervention arm (PediAppRREST arm) and the two control arms.

The statistician also creates opaque sealed envelopes externally marked with the team identification number and containing a paper slip, which indicates the arm allocation for that specific team. Team group allocation is concealed until the simulation sessions. Randomization of participants to teams, and teams to the arms, is performed with SAS 9.4 (SAS Institute Inc., Cary, NC, USA) for Windows.

Due to the nature of the cognitive support tools used in the trial, blinding of participants as well as of research staff involved in the simulation sessions and video reviewers, is not possible. However, blinding of the statistician performing data analysis will be ensured. Data analysis is expected to be finalized by February 2022.

### 3.4 Outcomes

#### 3.4.1 Primary outcome

The primary outcome of the study is the number of deviations from the PALS guidelines made by the teams during the management of a standardized simulated scenario of non-shockable PCA.

Deviations from PALS guideline recommendations are defined as delays and errors according to a novel checklist we derived from the previously published checklist by Wolfe et al[20], denominated c-DEV, by integrating it with evidence-based guidelines,[6-8,11] previously reported scoring tools,[40-43] and checklists.[37,44,45] We named our new modified checklist c-DEV15plus. It includes 15 items, which represent correct critical actions for paediatric resuscitation (Table 1).

**Table 1: c-DEV15plus items for non-shockable PCA simulation scenario**

1. CPR started within 30 seconds (s) from recognition of pulseless state
2. CPR board/rigid surface positioned underneath the manikin within 60 s from recognition of pulseless state
3. Compression/ventilation ratio 15:2
4. Help called (hospital emergency response system activated) within 60 s from recognition of pulseless state
5. Compressors switched more than once during CPR
6. ECG-monitoring started within 60 s from recognition of pulseless state
7. IV/IO access called within 60 s from recognition of pulseless state
8. First epinephrine called within 30 s from recognition of pulseless state
9. First epinephrine administered at the correct dose and dilutiona and by the correct route (IV or IO), followed by a normal saline flush, while compressions are being performed, within 300 s (5 minutes) from recognition of pulseless state
10. Second epinephrine called between 3 and 5 minutes from the first administration of epinephrine
11. Second epinephrine administered at the correct dose and dilutiona and by the correct route, followed by a normal saline flush, while compressions are being performed, within 5 min from the first epinephrine
12. Blood gas called during cardiac arrest
13. Reversible causes treated
14. Shock not administered
15. Medications other than adrenaline (e.g. amiodarone, lidocaine, atropine) not administeredb

---

*Abbreviations:* CPR=cardiopulmonary resuscitation; s= seconds; ECG=electrocardiogram; IV= intravenous; IO=intraosseous; min= minutes. *Note:* a Correct dose of epinephrine is defined as 0.01 mg/kg (or a deviation from the correct weight dose of less than 10%); correct dilution of epinephrine is defined as 1:10.000 (0,1 mg/ml); b Administration of medications to treat identified reversible causes is not considered in this item.

Each item of the c-DEV15plus is scored either as 0, when the action is performed correctly and timely, as described in the item, or as 1, when the action is not undertaken, undertaken incorrectly, or with wrong timing and, in the event of drug administration, when the dose, duration or route of administration is wrong. The sum of the points attributed to the items represents the c-DEV15plus total score, hence ranging from 0 to 15, with higher scores corresponding to a higher number of deviations from the guidelines. Outcome assessors will score the scenarios through the c-DEV15plus tool using the data registered and coded by the video reviewers.

### 3.4.2 Secondary outcomes

The following secondary outcome measures will be collected:

- *Performance and time to accomplish critical resuscitation interventions* recommended by PALS guidelines.[6-11,20] The interventions evaluated will be: (i) cardiac arrest recognition (pulselessness); (ii) start of chest compressions; (iii) start of ventilation; (iv) use of a CPR board or a rigid surface underneath the manikin; (v) call for emergency team help; (vi) start of EKG monitor; (vi) first epinephrine administration; (vii) second epinephrine administration; and (viii) treatment of reversible causes of CA. Performance and time to accomplish critical interventions (in seconds) during resuscitation will be assessed and recorded by video reviewers in the study CRFs and will be analysed both as time from the beginning of the scenario and as time from the recognition of pulselessness.
- *Usability of the app*. To assess the PediAppRREST app usability, the team leaders of the intervention group will be administered one validated questionnaire, the System Usability Scale (SUS).[46,47] Further, the team leader will be asked to complete a questionnaire with open-ended questions.
- *Team leaders' workload* measured by the validated, multidimensional NASA-Task Load Index (NASA-TLX).[48,49] This tool includes six subscale scores that represent independent clusters of variables and different domains of the perceived workload: Mental, Physical, and Temporal Demands, Frustration, Effort, and Performance.
- *CPR quality* measured by the Skill Reporter (Laerdal TM), the internal software of the manikin. CPR quality is defined as: i) proportion of chest compressions with depth 50-60 mm; ii) chest compression fraction (the percentage of time during CA with chest compressions), iii) mean chest compression depth; and iv) mean chest compression rate, according to AHA standards.[7,50]

- Team *resuscitation performance* as evaluated with the Clinical Performance Tool (CPT).[40,41] The CPT is a validated scoring system designed based on PALS algorithms, through which sequence, timing, and quality of specific actions, during different simulated scenarios, can be assessed. The CPT section for the asystole will be used to evaluate teams' performance.

### 3.5 Intervention

#### 3.5.1 Intervention arm - *PediAppRREST app*

The PediAppRREST, is an interactive, multimodal (audio-visual), “checklist” app, sequentially displaying prompts on recommended PCA management interventions.[37] It was specifically designed in 2019 to guide the team leader to perform resuscitation interventions in the sequence/timing and modality reported by the AHA PALS 2015 guidelines.[6-8]

The design and development of the app was guided by the results of a previous study conducted by our research team, which assessed deviations from guidelines in PCA simulation scenarios managed by paediatric residents.[38] The app was further refined following an iterative prototyping development approach with serial testing by our research staff, and according to the feedback provided by paediatric residents involved in a simulation-based pilot study.[37] The PediAppRREST app received a good usability evaluation and did not appear to increase team leaders' workload.[37]

Following the publication of the updated AHA PALS 2020 guidelines [11], the content and prompts of the app were checked against the guideline updated recommendations. Prompts to administer epinephrine as soon as possible and to guide post-arrest management were already provided by the app. The only content that required changing was the recommended ventilation rate for patients with an advanced airway from 1 breath every 6 seconds to 1 breath every 2 to 3 seconds. However, this last parameter is not included in the study outcomes, and it will not affect the results of our study.

#### 3.5.2 Control arm - *PALS pocket reference card*

The AHA PALS pocket reference card is a 10 cm x 16.5 cm, full-colour, 2-sided, 6-panel card that shows the AHA treatment algorithms.[51] By providing a quick reference tool, it serves as a cognitive aid for healthcare providers who either direct or participate in the management of paediatric respiratory and/or cardiovascular emergencies, including CA. The PALS pocket reference card is used during the PALS course and in a variety of healthcare settings. Although there is no published evidence on its effectiveness, the PALS reference pocket card by summarizing the content and sequence of recommended interventions, is the cognitive aid most

widely used worldwide. Participants were provided the 2015 AHA PALS reference pocket card [51] until the new 2020 AHA PALS reference pocket card [52] was available and introduced in the study in 2021. Participants in this arm are also allowed to use a pocket calculator to compute medication dosages/dilution and a timepiece.

### **3.5.3 Control arm - no cognitive aid**

Teams who are assigned to the CtrlPALS-group, are not able to use neither the PediAppRREST app nor the PALS pocket reference card to manage the simulated scenario. However, they will be allowed to use a pocket calculator to work out medication dosages/dilution and a timepiece, but no other cognitive tool.

## **3.6 Study procedures**

Participant recruitment and assessment will take place over a 15-month period (September 2020 – December 2021). The University Hospital of Padua is the coordinating centre of the trial. Its research team will oversee all study procedures and processes during the simulation sessions to assure standardised high-quality procedures are carried out at each participating centre (Padua, Florence, Novara, Rome). At the trial simulation sessions, the research staff meet the residents, illustrate the study, answer any possible questions, re-assess eligibility criteria for each participant, and obtain informed consent for study participation and video recording.

During all trial sessions measures to prevent COVID-19 infection spread (physical distancing, hand hygiene, use of personal protective equipment during the scenario, temperature and health checks, contact tracing, surfaces/mannequin/equipment disinfection, etc.) are strictly followed for participants and research staff's safety.[53,54]

Before beginning the simulation session, all teams watch the same 20-minute briefing video about the study procedures and orientation to the setting, manikin, and equipment. This phase has also the aim of increasing participants' adherence to intervention protocols and study procedures.

After the briefing, each team progressively receives and opens its assigned sealed envelope, which contains the arm allocation (PediAppRREST or CtrlPALS+ or CtrlPALS-). Thereafter, all participants wear a sticker with the corresponding team identification number and personal identification code. Ten minutes before their assigned simulated scenario each team is informed that the scenario will be about a PCA case, without specifying any further detail. The teams assigned to the intervention arm (PediAppRREST) watch a 5-minute tutorial video about the app and its use, prepared ad-hoc for this study. They are also given five minutes to practically

familiarize with the tablet and the app. The teams in the CtrlPALS+ arm are given five minutes before the scenario to familiarize with the PALS pocket algorithm card, while teams in the CtrlPALS- arm are given five minutes to discuss how to manage the scenario without any PALS-related cognitive aid.

Subsequently, each team participates in a 10-minute standardized intermediate-fidelity simulated scenario of non-shockable PCA caused by hypovolemia and hypoglycemia. A non-shockable rhythm was chosen for the simulated scenario because it is the most common initial cardiac arrest rhythm detected in PCA.[55] The setting, the equipment set up, the scenario, and the manikin (Resusci Junior QCPR Laerdal TM whose head is replaced with the MegaCodeKid Laerdal TM manikin's head, on which advanced air management can be performed) are the same for all the centres. The scenario is introduced by a standardized video where an actress, playing the patient's (manikin's) mother, provides essential clinical information (further scenario details are included in the Appendix 1). The scenarios are conducted off-site, in rooms set up to resemble the Emergency Department Shock room including regularly available equipment. The simulation rooms are set up in a standardized fashion between participating sites. Every team works with one confederate nurse and can call confederate consultants on the phone, who answer based on a standardized script. During the scenario, the team can speak with a facilitator, who is a member of the research team and answers participants' questions following a pre-determined script.

All the scenarios are video-recorded by two different fixed cameras with standardized positions that point to the team and to the monitor. An additional camera captures the actions of the team leaders who use the PediAppRREST app, framing the screen of the tablet. Only the videos from the two fixed cameras will be evaluated by the reviewers. The videos of the team leaders' actions with the tablet will be examined only by the research team to assess potential bugs in the app or challenges with its use.

After the scenario, all participants complete a demographic survey reporting their sex, age, year and type of residency program, experience in simulation and resuscitation, and time from PALS/P-BLS/BLS/ALS/ACLS certification. In addition, all the team leaders complete the NASA-TLX and the team leaders in the intervention arm also evaluate the app usability, by completing the SUS. Subsequently, all participants participate in a 15-minute debriefing during which they receive feedback about their performance, and the teams in the intervention arm are able to provide feedback about the app. During this phase, the debriefer reports the feedback received on the app in a specific CRF.

The videos of the scenarios will be evaluated by two independent, and previously trained, reviewers expert in paediatric emergency medicine and simulation. Training of the reviewers, on

RCT-unrelated PCA simulation videos, will be conducted by the principal investigator (FC), until the reviewers will reach at least 80% inter-rater agreement with the principal investigator. No more than two weeks will lapse between the training and the assessment of the RCT videos. The reviewers will use a standardized data collection form where actions performed by the team and time to performance will be assessed and recorded. Disagreements between reviewers will be resolved by consensus with a third independent reviewer, expert in paediatric emergency medicine and simulation. Inter-rater reliability between reviewers will be monitored and reported. Data pertaining the CPR quality from the manikin software will be extracted and recorded on a specific CRF. The scores on the c-DEV15plus, and all the secondary outcomes will be calculated by outcome assessors based on the data coded and reported by the video reviewers on the CRFs.

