### **3.8.2 Data analysis plan**

The results will be summarized for each study group with counts and percentages for categorical variables, mean and standard deviation (SD) or median and interquartile range for quantitative variables, as appropriate. The normality of the quantitative variables will be checked with the Shaphiro-Wilk test.

The c-DEV15plus scale, the performance and time to accomplish specific resuscitation interventions, NASA-TLX, CPT and cardiopulmonary resuscitation metrics will be compared between groups with one-way ANOVA model, followed by the Tukey-Kramer multiple comparisons adjustment procedure in case of statistical significance.

The outcomes will also be analysed with a linear mixed model considering the team as a cluster to evaluate the influence of participants' characteristics on the outcome. To take into account the correlation of the observations within a team, we will specify an undetermined correlation matrix. In case of a not normal distribution of the model residuals, we will proceed with a transformation in order to normalize the distribution.

Both intention-to-treat and per-protocol analyses will be performed.

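### Self-reported experience and recalled time since certification are collected only after allocation is known and the scored scenario is over, although a mixed model is planned to relate participants' characteristics to the outcome.

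*Protocol*

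**What the plan says.** Protocol section 3.6 sets the order of a session. Staff first "re-assess eligibility criteria for each participant, and obtain informed consent for study participation and video recording". A briefing video follows, and then "each team progressively receives and opens its assigned sealed envelope, which contains the arm allocation". Next come the arm-specific familiarisation and the 10-minute scored scenario. Only then does the survey appear: "After the scenario, all participants complete a demographic survey reporting their sex, age, year and type of residency program, experience in simulation and resuscitation". It also asks for the interval since the resuscitation certificate was obtained. The debriefing comes last.

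Section 3.3 states that "blinding of participants as well as of research staff involved in the simulation sessions and video reviewers, is not possible".

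Section 3.8.2 describes two analyses that matter here. The outcomes "will be compared between groups with one-way ANOVA model"; this comparison uses no survey item. A linear mixed model is then added "to evaluate the influence of participants' characteristics on the outcome".

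**The concern.** An explanatory variable should be measured before the outcome it is meant to explain, and in a randomised trial preferably before allocation is known. Here the experience items are answered by unblinded residents minutes after a performance of which they have their own impression. A resident whose team struggled may report less experience than the same resident would have reported an hour earlier. One who was prompted step by step by the app, or who worked with no aid, may also answer differently.

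Two results are exposed. The first is any mixed-model estimate relating experience, or time since certification, to deviations. The second is the description of experience by arm, which readers use to judge whether randomisation produced comparable groups.

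**Working it through.** No figure in the protocol depends on this point, so there is nothing to recompute. The check sets the order of procedures against the use of the data.

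**1. Order of events (sections 3.3 and 3.6).** Eligibility re-check and consent → briefing → envelope opened → familiarisation → scored scenario → survey → debriefing. Every survey answer therefore follows both the exposure and the outcome. It precedes the formal feedback.

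**2. What is known before allocation, item by item.**

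| Characteristic | Established before the envelope is opened? | Can arm or performance plausibly change the answer? |
|---|---|---|
| Specialty | Yes: teams are "stratified by study site and residency program specialty" (3.3) | No |
| Certification status | Yes: an eligibility criterion (3.2), used to form teams and choose the leader (3.3) | No |
| Sex, age, year of residency | No earlier collection described | Hardly |
| Time since certification | No earlier collection described | Somewhat, if recalled and not taken from a certificate |
| Experience in simulation and resuscitation | No earlier collection described | Yes, to a degree that depends on how the items are worded |

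The exposure narrows to the last two rows, mainly the last.

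**3. Use of the items (section 3.8.2).** The one-way ANOVA compares arms without covariates, so post-scenario answers cannot enter it. The mixed model is meant to examine participants' characteristics. The protocol excludes none of them, and the post-scenario survey is the only source it describes for experience and time since certification.

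**4. How a spurious association could arise.** Suppose true experience had no influence on deviations.
- If poor performance lowers reported experience, teams with more deviations contain residents reporting less experience. The model would then show experience as protective, although the direction is the reverse.
- If the arm shifts both deviations and reported experience, the two are associated across arms without either causing the other.
- In the description of the arms, a difference in reported experience could be chance imbalance or a reporting effect. Data collected at this point cannot separate them.

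**5. Size.** The survey is given to all 315 planned participants, but only the experience items and recalled certification time are at risk. The protocol gives neither the wording of the items nor any data on how such answers shift after a scenario, so no magnitude or range can be derived.

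**The case against.** The strongest reply is that little of substance is exposed. The primary comparison does not use the survey. Specialty and certification status are known beforehand. The form is not shown, so the experience items may ask for counts of simulations or arrests attended, which a 10-minute scenario would hardly alter. No covariates are listed in section 3.8.2, and that list is commonly left to an analysis plan. The survey precedes the debriefing, so formal feedback cannot colour it. Asking about resuscitation experience beforehand might also prime teams, who learn only ten minutes ahead that the case is a cardiac arrest.

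Most of this stands and limits the weight of the point. It does not remove it. Factual items still carry recall error, and a team has its own impression of how it did before any debriefing. An analysis plan can choose covariates but cannot change when a form was completed. The priming argument is weak, because the study is explained and resuscitation certification re-checked at the same early contact.

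A reader might infer four stronger things that the protocol does not support:
- **That the arm effect is distorted by adjustment.** Section 3.8.2 does not say the mixed model adjusts the comparison of arms; its stated purpose is to study characteristics.
- **That experience is rated on a subjective scale.** The text says only that it is reported.
- **That the survey delays the team leader's NASA-TLX.** Section 3.6 mentions the questionnaire as an addition and fixes no order between the two forms.
- **That teams with an aborted scenario would lack baseline data.** No aborted scenario is described; Appendix 1 has the scenario run its full length whatever the team does. The losses anticipated in section 3.8.1 are technical or procedural, and a failed recording does not prevent a survey.

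**Conclusion.** The point holds in a narrow form and is minor. Experience in simulation and resuscitation, and recalled time since certification, are collected after both allocation and outcome, although a suitable contact before allocation already exists. Mixed-model findings on these items could partly reflect reverse causation, and their description by arm could partly reflect reporting.

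This rests on two assumptions: that these items are among the characteristics entered in the mixed model, which the protocol permits but does not spell out; and that answers are open to some influence from the session. If the items prove to be purely factual and checked against records, little remains. The primary result, the sample size and the error rate are untouched.

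**What to change.** **Remaining sessions.** Give the survey at the consent and eligibility re-check, before the envelope is opened, and record certification type and date there. Staff already meet every resident at that step, so this moves one form within the same session and adds one recorded date. No sample size, significance level or outcome changes.

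**Sessions already held.** Section 3.5.2 indicates that some had taken place, since the pocket card was replaced during the study. Take certification dates from records where available. Report mixed-model results for post-scenario experience items as exploratory, and add a sensitivity analysis limited to characteristics that are fixed or known before allocation: sex, age, year, specialty, certification type and, where documented, certification date. Beside the description of the arms, state when the experience items were collected.

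**Cost.** After the change, the experience items will have been collected at two different times across the trial. Record the timing for each team so that the two sets can be told apart in the analysis. Any contrast between them will also carry calendar time, so it cannot by itself measure the reporting effect. If no sessions remain, only the analytic part applies.
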